# A randomized phase II trial to elucidate the efficacy of capecitabine plus cisplatin (XP) and S-1 plus cisplatin (SP) as a first-line treatment for advanced gastric cancer: XP ascertainment vs. SP randomized PII trial (XParTS II)

**DOI:** 10.1186/1471-2407-12-307

**Published:** 2012-07-23

**Keywords:** Biomarker, Capecitabine, Cisplatin, Clinical trial, Gastric cancer, S-1

## Abstract

**Background:**

On the basis of international clinical trials, capecitabine plus cisplatin (XP) as a first-line treatment of advanced gastric cancer is considered a global standard regimen. However, the usefulness of XP as compared with S-1 plus cisplatin (SP), which is considered standard therapy in Japan, has not yet been assessed.

**Methods/design:**

This is a multicenter randomized phase II trial to elucidate the efficacy of XP as compared with SP for first-line treatment of advanced gastric cancer. Patients with unresectable metastatic or recurrent gastric cancer, 20–74 years of age and human epidermal growth factor 2 (HER2)-negative status, will be assigned in a 1:1 ratio to receive either S-1 40 mg/m^2^ bid for 21 days plus cisplatin 60 mg/m^2^ (day 8) every 5-week cycle or capecitabine 1000 mg/m^2^ bid for 14 days plus cisplatin 80 mg/m^2^ (day 1) every 3-week cycle. Patients will be also asked to the analysis of tumor tissues for translational investigations. The Primary endpoint is progression-free survival and secondary endpoints are overall survival, time to treatment failure, tumor response rate and safety. These comparisons will also be evaluated in terms of biomarkers. Planned sample size is 100 (50 in each arm), which is appropriate for this trial.

**Discussion:**

Fluoropyrimidine plus cisplatin combination is the standard regimen of the first line treatment for advanced gastric cancer. Both S-1 and capecitabine are the prodrug of 5-FU but differ from their process of metabolism. Result of this trial and translational research will provide the important clues to prepare the individualized therapy for advanced gastric cancer in the near future.

**Trial registration:**

ClinicalTrials.gov Identifier NCT01406249

## Background

Gastric cancer is the fourth most common malignancy in the world (988 602 cases in 2008, 7.8% of total) and the second leading cause of cancer death (737 419 deaths, 9.7% of total)
[1]. For the treatment of advanced or recurrent gastric cancer (AGC), the most commonly used regimens are combination chemotherapy consisting of a fluoropyrimidine (5-fluorouracil or oral fluoropyrimidine) plus a platinum agent with or without docetaxel or anthracyclines
[2-6].

S-1 is an oral anticancer drug composed of the 5-fluorouracil (5-FU) prodrug tegafur and two 5-FU modulators; it has achieved high response rates in patients with gastric cancer in phase II studies
[7,8]. In a phase III trial (SPIRITS trial) that compared S-1 alone to S-1 plus cisplatin (SP), SP showed a significantly longer overall survival (OS; 13 months vs. 11 months; HR = 0.77, 95% CI 0.61–0.98, p = 0.04) and longer progression-free survival (PFS; 6.0 months vs. 4.0 months; HR = 0.57, 95% CI 0.44–0.73, p < 0.0001)
[4]. Therefore, SP is now considered to be one of the standard first-line regimens for AGC in Japan.

Capecitabine is also an oral fluoropyrimidine, which is metabolized primarily in the liver and converted in tumor tissues to 5-FU by the enzyme thymidine phosphorylase (TP), which is associated in higher concentrations in tumor cells than in normal cells
[9]. Kang and colleagues evaluated the non-inferiority of capecitabine plus cisplatin (XP) compared with 5-FU plus cisplatin (FP). The median PFS showed significant non-inferiority (5.6 months vs. 5.0 months; HR = 0.81, 95% CI 0.63–1.04, P < 0.001)
[5]. On the basis of these results, XP is now considered one of the standard treatments of AGC
[10], and XP was adopted as the reference arm in two recent global studies of molecular targeting agents
[11,12]. However, data is scarce with respect to XP treatment in Japanese patients, and also the usefulness of XP as compared with SP has not yet been assessed.

As another issue, these 2 types of oral fluoropyrimidine show some different characteristics in the mechanisms of their antitumor effect. A subset analysis of the FLAGS trial showed that S-1 seemed to be better than 5-FU in the subgroup with diffuse-type gastric cancer
[6]. This result was consistent with the results of a subset analysis of the JCOG9912 trial, which showed that S-1 was better than 5-FU in patients with diffuse-type gastric cancer or with gastric cancer associated with high dihydropyrimidine dehydrogenase (DPD), with diffuse-type tumors associated more commonly than intestinal type with high DPD
[13]. This result was expected, since S-1 consists of tegafur, otastat potassium, and gimestat which is a potent competitive inhibitor of DPD. Capecitabine is transformed to 5-FU in several steps, to be finally converted by TP as above
[9]. A phase II trial in Japan showed that response rate (RR) was significantly higher (Fisher’s exact test, *p* = 0.028) in patients with TP-positive and DPD-negative tumors (60%, 6/10) than in the remaining patients (13%, 2/15)
[14]. In contrast, high expression of TP is reported to be negatively associated with efficacy of 5-FU or S-1 in gastric cancer
[15,16].

On the basis of the above reports, histological type (diffuse or intestinal) and biomarkers (TP, DPD, and others) may be candidates to select whether S-1 or capecitabine be used for each patient, although validation with a randomized study is necessary. We planned the current clinical trial to elucidate the efficacy of XP and SP for the first-line treatment of AGC. This comparison will be also evaluated in terms of several biomarkers.

## Method/design

### Study objective

This randomized phase II trial is planned to elucidate the efficacy of SP and XP and also to explore predictive or prognostic biomarkers with additional research. This trial protocol has been approved by the Institutional Review Board (IRB) of each participating institution and the Kanagawa Cancer Center.

### Study endpoints

Primary endpoint is PFS and secondary endpoints are OS, RR, time to treatment failure (TTF), and incidence of adverse events (safety).

### Eligibility criteria

#### Inclusion criteria

(i) Histologically confirmed gastric adenocarcinoma with unresectable metastatic or recurrent disease

(ii) Lesions confirmed by imaging no more than 28 days before registration (not required for measurable lesions as defined in RECIST version 1.1)

(iii) No previous chemotherapy or radiotherapy. However, prior adjuvant chemotherapy is allowed if more than 6 months has passed since the end of adjuvant chemotherapy

(iv) Eastern Cooperative Oncology Group (ECOG) Performance Status of 0, 1, or 2

(v) Life expectancy of at least 3 months after registration

(vi) Written informed consent

(vii) Between the ages of 20 and 74 years at the time informed consent is obtained

(viii) Adequate major organ function including:

(a) Neutrophil count: ≥1500/mm^3^

(b) Platelet count: ≥10.0 × 10^4^/mm^3^

(c) Hemoglobin: ≥9.0 g/dL

(d) AST, ALT: ≤2.5 × upper limit of normal (ULN) in each institution (≤5 times in cases of metastases to liver)

(e) ALP: ≤2.5 × ULN in each institution (≤5 times in cases of metastases to liver, and ≤10 times in cases of metastases to bone)

(f) Total bilirubin: ≤1.5 × ULN in each institution

(g) Creatinine clearance: ≥60 mL/min (as estimated by Cockcroft-Gault equation)

#### Exclusion criteria

(i) HER2- positive status

(ii) Previous history of fluoropyrimidine therapy within 6 months prior to registration

(iii) Previous treatment with platinum agents within 12 months prior to registration

(iv) Previous treatment with cisplatin more than total dose of 120 mg/m^2^

(v) Previous history of serious hypersensitivity to fluoropyrimidines or platinum agents

(vi) Previous history of adverse reactions suggestive of dihydropyrimidine dehydrogenase (DPD) deficiency

(vii) More than 1 cancer at the same time or more than 1 cancer at different times separated by a 5-year disease-free interval. However, multiple active cancers do not include carcinoma *in situ* or skin cancer which is determined to have been cured as a result of treatment.

(viii) Obvious infection or inflammation (pyrexia ≥38.0°C)

(ix) Active hepatitis

(x) Heart disease that is serious or requires hospitalization, or history of such disease within the past year

(xi) Having a complication that is serious or requires hospitalization (intestinal paralysis, intestinal obstruction, interstitial pneumonia or pulmonary fibrosis, poorly controlled diabetes mellitus, renal failure, liver disorders, or hepatic cirrhosis)

(xii) Being treated or in need of treatment with flucytosine, phenytoin, or warfarin potassium

(xiii) Chronic diarrhea (watery stools or ≥4 times/day)

(xiv) Active gastrointestinal bleeding

(xv) Body cavity fluids requiring drainage or other treatment

(xvi) Clinical suspicion or previous history of metastasis to brain or meninges

(xvii) Women who are pregnant, breastfeeding, or potentially (hoping to become) pregnant

(xviii) Unwillingness to practice contraception

(xix) Poor oral intake

(xx) Psychiatric disorders which are being, or may need to be, treated with psychotropics

(xxi) Otherwise determined by investigators or site principal investigators to be unsuitable for participation in study

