8.)	In cases where progression is diagnosed on the basis of imaging, the event will be determined based not on evaluation dates where the result is “suspected” on imaging but on a subsequent evaluation date where progression is “confirmed” on imaging.
9.)	Secondary cancer (multiple cancers in metachronous) will not be regarded as either an event or censored.

The primary objective of this trial is to evaluate the PFS of SP and XP as the first-line treatment for advanced gastric cancer. The 24-week progression-free rate (PFR) will be estimated for each group, calculating point estimates and 2-sided 90% confidence intervals. The 2-sided 90% confidence interval of the difference between the 2 groups will be also estimated. Exploratory analysis will be done to test the null hypothesis that PFS is equal in both groups. Cumulative PFS curves will be constructed as time-to-event plots by the Kaplan-Meier method.

With respect to secondary endpoints, efficacy endpoints OS and TTF will be evaluated according to the method of analysis of the primary endpoint. Overall response rate (RR) is defined as the proportion of patients with complete response (CR) or partial response (PR) by RECIST out of the patients with measurable lesions, and the chi-square test will be used to compare the 2 groups. The 2-sided 95% confidence interval of the difference between the 2 groups will also be estimated. For the analysis of safety, Fisher’s exact test will be used if necessary, and the exact confidence intervals for the binomial distribution will be estimated.

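### As written, the metachronous part of exclusion (vii) runs the wrong way: it bars another cancer followed by 5 disease-free years and does not bar a more recent one

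*Protocol article*

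**What the plan says.** The rule is item (vii) of the list headed "Exclusion criteria" in the protocol article, so a patient who meets it is ineligible. Its first sentence describes "More than 1 cancer at the same time or more than 1 cancer at different times separated by a 5-year disease-free interval". Its second sentence provides exceptions, stating that "multiple active cancers do not include carcinoma" in situ, or skin cancer judged to have been cured by treatment.

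Three other places bear on the same patients:

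- Inclusion (iii): "No previous chemotherapy or radiotherapy", with an allowance for adjuvant chemotherapy that ended more than 6 months earlier.
- Exclusion (xxi), a discretionary clause: "Otherwise determined by investigators or site principal investigators to be unsuitable for participation in study".
- Table 1, item 9, on the primary endpoint: "Secondary cancer (multiple cancers in metachronous) will not be regarded as either an event or censored". Item 1 of the same table counts death from any cause as a PFS event.

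**The concern.** A rule on multiple cancers in an exclusion list serves to keep out patients whose other cancer may still affect their outcome. The second sentence of (vii) says as much by speaking of active cancers. A cancer followed by 5 disease-free years is hard to call active, yet that is the group which the first sentence names for exclusion. A patient whose other cancer was treated more recently, for instance 2 years ago, is neither a simultaneous case nor one separated by the stated interval, so the words do not reach that patient.

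Two things are at stake. First, this is a multicentre trial. Some institutions may apply the literal words and others the apparent intent, so eligibility could differ between sites, and a reader of the published criteria would misjudge who was enrolled. Second, a recently treated other cancer can cause death or produce lesions. Death from it counts in PFS and OS, and a lesion wrongly attributed to gastric cancer would count as progression.

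**Working it through.** No formula applies, because the point does not depend on any figure in the plan. The check takes each type of patient through the literal words of (vii) and then compares the result with the second sentence.

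| Other cancer | Simultaneous limb met? | 5-year limb met? | Result under first sentence | Fits a target of active cancers? |
|---|---|---|---|---|
| Present at the same time | Yes | Not needed | Excluded | Yes |
| Earlier, disease-free interval under 5 years | No | No | Not excluded | No |
| Earlier, disease-free interval of 5 years or more | No | Yes | Excluded | No |

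The first row behaves as expected. The other two are reversed relative to the second sentence. No word such as within, less than or unless accompanies the interval to turn it round, and the rule is not restated anywhere else in the article.

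The next question is whether another criterion repairs the second row.

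- Inclusion (iii) removes patients whose recent other cancer was treated with radiotherapy or with chemotherapy outside the adjuvant allowance. It does not remove a patient treated by surgery alone.
- Exclusion (xxi) lets an investigator decline a patient, but it sets no rule and cannot make institutions consistent.

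For the third row, no criterion readmits the long disease-free patients whom (vii) excludes.

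Last, the link to the endpoints. Under Table 1 item 9 a metachronous cancer is by itself neither a PFS event nor a reason to censor. Two routes remain open: death from that cancer, which item 1 counts as a PFS event and which also counts in OS, and a lesion from it that is read as gastric progression.

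The inputs to the sample-size section (24-week progression-free rates of 40% and 55%, the error rates and power, the registration and follow-up periods, and the biomarker assumptions) do not involve (vii). Sample size and power therefore do not change.

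**The case against.** The strongest reply is that this is a wording slip in a condensed article. The text that sites work from is the full protocol and the Case Registration Form, neither of which is shown. Enrolment began in July 2011 and the article appeared in July 2012, so patients had been registered for about a year before this sentence was published. A screening physician can also recover the intent from the second sentence. Much of this stands: a slip is the likely cause, and nothing shows that the registration form repeats it. It does not dispose of the point. The sentence is a stated eligibility rule that gives the wrong result if followed, and it conflicts with the sentence beside it. It is not a detail left to a fuller document.

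Stronger readings are tempting, and the documents do not support them.

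- A reader might infer that each wrongly admitted patient shifts an arm's 24-week progression-free rate by 1/50 = 2 percentage points, to be set against the planned 55 − 40 = 15 points. That shift needs a misattributed event before 24 weeks in a patient who would otherwise have been progression-free then. The article gives neither the frequency of recent other cancers nor the chance of such an event.
- A reader might infer that the whole criterion is inverted. The simultaneous limb is not.
- A reader might infer that Table 1 item 9 covers only cancers arising after entry. It does not say so; its scope is metachronous cancers, which arguably includes the disputed group. It gives partial protection, short of death from the other cancer and misread lesions.
- A reader might infer that suitable patients were in fact turned away. The article contains nothing on how (vii) was applied.

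**Conclusion.** The point holds in a limited form. The metachronous limb of exclusion (vii) is wrong in direction as written and contradicts the criterion's own second sentence; inclusion (iii) and exclusion (xxi) close the gap only in part. The likely effect is small: possible inconsistency of screening between institutions, a published criterion that misdescribes the population, and an occasional death or lesion from another cancer entering PFS or OS. The size of any effect on the progression-free rate cannot be derived from the article.

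The conclusion rests on two assumptions: that a separation of 5 years includes longer intervals, and that the second sentence expresses the purpose of the rule. The article does not state which wording was intended, so the full protocol must settle it.

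**What to change.** Reconcile the two sentences of (vii) with the full protocol and the registration form, and state the direction of the 5-year interval explicitly. To agree with the second sentence, the metachronous limb would refer to another cancer with a disease-free interval shorter than 5 years. Leave the simultaneous limb and the carcinoma in situ and skin cancer exceptions as they are.

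Because enrolment was already under way, also check how patients registered so far were screened on this item, and describe the rule as it was actually applied when the trial is reported.

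The cost is one phrase in the criterion, a matching correction to the registration form if it carries the same wording, and a short review of existing registrations. No extra patients, trial procedures or changes to the analysis are needed.

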### Registration

Physicians or coordinators will send a Case Registration Form to the data center (Epidemiological and Clinical Research Information Network, ECRIN) with all the required items filled out. Enrollment has started from July 2011.

### Startification

Eligible patients will be randomized to either Arm-A (SP treatment) or Arm-B (XP treatment) by dynamic allocation via a centralized randomization method using 5 stratification factors as balancing variables:

(i) baseline ECOG Performance Status (0–1/2)

(ii) measurable lesion (yes/no)

(iii) prior adjuvant chemotherapy (yes/no)

(iv) histopathological classification (intestinal/diffuse)

(v) institution.

### Statistical analysis

PFS has been set as the primary endpoint and is defined as the time from date of registration until the date that progression is determined or the date of death for any reason, whichever is sooner. “Progression” will be evaluated on the basis of Response Evaluation Criteria In Solid Tumors (RECIST) version 1.1
[17]. More information about the definition of PFS and Progression are pre-specified (Table
1).

**Table 1 T1:** Definition of PFS and progression

**Definition of PFS and progression are predefined as below**	
1.)	PFS will be determined as the time from the date of registration until the date that progression is determined or the date of death for any reason, whichever is sooner.
2.)	“Progression (PD)” means both PD confirmed by routine diagnostic imaging in each course and PD confirmed by as-needed diagnostic imaging in the case that there is clinical suspicion of PD. In the latter case, it is preferable that there is at least objective evidence.
3.)	When progression is determined based on diagnostic imaging, the date of progression will be the date on which imaging is assessed. When clinical progression is first determined independently of diagnostic imaging, and then later objectively determined on the basis of diagnostic imaging, the date of progression will be back-dated to the date of determination of clinical progression. If no objective evidence is obtained, it will be treated as a censoring event in the formal analysis, and sensitivity analysis will be also conducted as if this were PD.
4.).	When considering tumor regrowth and determining PD according to RECIST, it is considered a PD as PFS event regardless of tumor diameter. But even if it is decided as PD according to RECIST, investigators can continue the protocol treatment if they consider continued treatment to be beneficial to the patient.
5.)	If treatment discontinuation is needed due to symptomatic deterioration without any objective evidence at that time, it is reported as “symptomatic deterioration”. Investigators should endeavor to obtain objective evidence of the progression even after discontinuation of treatment. In this case, the event shall be judged to be clinical PD and handled as mentioned in 2) above. When progression is determined on the basis of diagnostic imaging, the date of progression will be back-dated to the date of diagnosis of symptomatic deterioration.
6.)	Survivors for whom progression has not been determined will be censored based on the last date on which the absence of progression was clinically confirmed (the last day that PFS was confirmed).
7.)	Cases of discontinuation of protocol treatment because of toxicity or patient refusal, even if another therapy is added as a post-treatment, will be censored at the date of discontinuation or the date that post-treatment was started.
8.)	In cases where progression is diagnosed on the basis of imaging, the event will be determined based not on evaluation dates where the result is “suspected” on imaging but on a subsequent evaluation date where progression is “confirmed” on imaging.
9.)	Secondary cancer (multiple cancers in metachronous) will not be regarded as either an event or censored.

The primary objective of this trial is to evaluate the PFS of SP and XP as the first-line treatment for advanced gastric cancer. The 24-week progression-free rate (PFR) will be estimated for each group, calculating point estimates and 2-sided 90% confidence intervals. The 2-sided 90% confidence interval of the difference between the 2 groups will be also estimated. Exploratory analysis will be done to test the null hypothesis that PFS is equal in both groups. Cumulative PFS curves will be constructed as time-to-event plots by the Kaplan-Meier method.

With respect to secondary endpoints, efficacy endpoints OS and TTF will be evaluated according to the method of analysis of the primary endpoint. Overall response rate (RR) is defined as the proportion of patients with complete response (CR) or partial response (PR) by RECIST out of the patients with measurable lesions, and the chi-square test will be used to compare the 2 groups. The 2-sided 95% confidence interval of the difference between the 2 groups will also be estimated. For the analysis of safety, Fisher’s exact test will be used if necessary, and the exact confidence intervals for the binomial distribution will be estimated.

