### Sample-size calculation

Assuming a threshold 24-week PFR of 40% and an expected 24-week PFR of 55% (clinically promising), and a 1.5-year registration period and a 1.5-year follow-up period, 49 patients are required in each group to ensure a 1-sided alpha of 5% and statistical power of 90%. Assuming that the 24-week PFR of the biomarker-positive (any FU-related enzyme or expression of intestinal type) population in the SP arm is 45%, and the risk reduction rate in the XP arm is 40%, 46 patients in total are needed to ensure a 2-sided alpha of 10% and statistical power of 70%. Under the hypothesis that the targeted biomarker-positive population is 50%, 92 patients in total are required. Considering the likelihood of some ineligible cases in the whole setting outlined above, the total sample size is set to 100. A following Phase III study will be designed for both randomized comparison and biomarker-oriented comparison of XP and SP (4 groups).

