### Follow-up

During treatment under this protocol, patients will have a physical check-up and a blood examination before every drug administration. PFS and RR will be monitored by using abdominal CT or MRI every 6 weeks and by measuring levels of tumor markers CEA and CA19-9.

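### Table 1 item 6 lets a clinical date without a scan extend progression-free time, so the 24-week PFR can be biased upward, by a small amount, if scans are missed before early loss to follow-up

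*Protocol article*

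**What the plan says.** All references are to the protocol article.

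- **Censoring.** Statistical analysis, Table 1 item 6 sets this rule: "Survivors for whom progression has not been determined will be censored based on the last date on which the absence of progression was clinically confirmed". A parenthesis restates this as the final day of confirmed PFS. It does not name the assessment that confirms it.
- **Event.** The text above Table 1: "Progression” will be evaluated on the basis of Response Evaluation Criteria In Solid Tumors (RECIST) version 1.1". Item 2 ties progression to routine or as-needed imaging and calls objective evidence preferable where the suspicion is clinical. Item 3 censors clinical progression that never obtains objective evidence, and adds a sensitivity analysis that counts it as progression. Item 8 waits for imaging confirmation when an image is only suspicious. Death from any cause is an event (item 1).
- **Other exits.** Stops for toxicity or refusal are censored under item 7, not item 6.
- **Calendar.** Follow-up: "patients will have a physical check-up and a blood examination before every drug administration". The next sentence sets abdominal CT or MRI every 6 weeks for monitoring PFS and response.
- **Use.** The PFS analysis estimates the 24-week PFR in each group, "calculating point estimates and 2-sided 90% confidence intervals". The Sample-size calculation rests on the same quantity, with a 40% threshold and a 55% expected rate.

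**The concern.** The two sides of the endpoint use different evidence. A clinical judgement that the patient is free of progression can extend event-free time. A clinical judgement that the patient has progressed, without imaging or death, does not produce an event in the formal analysis. Item 3 itself uses the word clinical in contrast to imaging, so a data manager could defensibly enter a visit date under item 6.

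Take a patient with stable disease at the week-18 scan who misses the week-24 scan, attends clinic to week 26 and is then lost. Read literally, item 6 censors this patient at week 26. The patient stays in the week-24 risk set with almost no chance of becoming an event. Item 3's sensitivity analysis does not help, because nobody declared clinical progression. What is at stake is a small upward shift in the main summary of the primary endpoint, and inconsistent coding across institutions.

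**Working it through.** **1. The plan's own figure.** Inputs from the Sample-size calculation: "Assuming a threshold 24-week PFR of 40% and an expected 24-week PFR of 55" per cent; "49 patients are required in each group to ensure a 1-sided alpha of 5% and statistical power of 90" per cent; "a 1.5-year registration period and a 1.5-year follow-up period". A one-sample exponential test on the log hazard, each arm against the threshold, reproduces the 49:

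- Weekly hazards: −ln(0.40)/24 = 0.0382 and −ln(0.55)/24 = 0.0249. Hazard ratio 0.652, ln = −0.427.
- Event probabilities with 78 weeks' uniform accrual plus 78 weeks' follow-up: P0 = 0.984, P1 = 0.937.
- n = (1.645/√0.984 + 1.282/√0.937)² / 0.427² = 48.8, so 49.

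The censoring date in item 6 does not enter this formula.

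**2. Who can be affected.** Minimum potential follow-up is 1.5 × 52 = 78 weeks, so nobody is administratively censored before week 24. Item 6 can move the 24-week PFR only through early loss to follow-up, or loss soon after a missed week-24 scan. Toxicity and refusal stops (item 7), deaths, and patients later scanned and found progressed are outside it.

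**3. One affected patient.** At a 24-week PFR of 55% (exponential), the risk per 6-week interval is 1 − 0.55^(1/4) = 0.139. With 49 patients, 49 × 0.55^(3/4) = 31.3 remain at risk after week 18, where the survival estimate is 0.639.

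- Last-scan censoring removes the patient: 30.3 × 0.139 = 4.21 expected events among 30.3, giving 0.639 × (1 − 4.21/30.3) = 0.550.
- Item 6 keeps the patient in the denominator: 0.639 × (1 − 4.21/31.3) = 0.553.

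The shift is about 0.3 points, which is also 0.139 × (1/49). A full 1/49 = 2.0 points would apply only if that patient had certainly progressed.

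**4. Simulation.** 200,000 patients per scenario; exponential PFS; scans every 6 weeks; visits every 3 or 5 weeks; 15% of events dated clinically or as deaths. Assumptions not in the document: loss by week 24 of 5–20%, and a clinic-only period before loss of 0, 6 or 12 weeks. The table gives the Kaplan-Meier 24-week PFR minus its no-loss value, in percentage points, at a true PFR of 55% with scan dates varying by ±1 week. The no-loss values are near 59% because progression is dated at the scan and some week-24 scans fall after week 24.

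| Scan gap before loss | Item 6 | Last-scan censoring |
|---|---|---|
| None | −0.06 (0.5896 − 0.5902) to −0.55 (0.5850 − 0.5905) | −0.16 (0.5886 − 0.5902) to −0.98 (0.5807 − 0.5905) |
| 6 weeks | +0.18 (0.5917 − 0.5899) to +1.09 (0.6021 − 0.5912) | −0.24 (0.5875 − 0.5899) to −1.15 (0.5797 − 0.5912) |
| 12 weeks | +0.55 (0.5964 − 0.5909) to +2.73 (0.6158 − 0.5885) | −0.31 (0.5878 − 0.5909) to −1.40 (0.5771 − 0.5911) |

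With no loss, both rules give the no-loss value exactly. A repeat simulation gave −0.1 to −0.5, +0.2 to +1.1 and +0.6 to +2.9 for item 6. The most extreme runs had a true PFR of 40%, 20% loss and scans on exact dates: +1.8 (0.4186 − 0.4003) for a 6-week gap and +4.1 (0.4406 − 0.3998) for 12 weeks. Measured directly against last-scan censoring over all runs, item 6 was higher by 0.0–0.6 points with scans kept, 0.3–2.6 with a 6-week gap and 0.8–4.9 with a 12-week gap.

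**5. Scale.** The 90% interval half-width at 55% with 49 patients is 1.645 × √(0.55 × 0.45/49) = 0.117, or 11.7 points.

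**The case against.** The strongest defence is that item 6 can be read as an imaging rule. Its parenthesis speaks of the day PFS was confirmed, and Follow-up says PFS is monitored by CT or MRI every 6 weeks. That reading is available but not secured, because the parenthesis is circular and item 3 sets clinical against imaging. The date rule is stated in a table described as pre-specified, so it is not a gap left to an analysis plan.

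The defence is right on several other points. Item 6 reaches few patients. The larger shifts need scan gaps that depart from the stated schedule. It would be too absolute to say that progression must always be shown by imaging: death counts, confirmed clinical progression is back-dated, and a sensitivity analysis counts unconfirmed clinical progression. Last-scan censoring is not bias-free either. It fell 0.2 to 1.4 points below the no-loss value in the table, and 1.6 points below in the worst run (0.4294 − 0.4452). Choosing between the conventions is partly preference.

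A reader might also infer a bias between arms, because visits follow drug administration and the cycles differ. The document does not support that. The scan interval is the same in both arms, and it gives no loss or missed scans by arm. At equal loss and equal gaps, changing only the visit interval between 5 and 3 weeks moved the item 6 shift by less than 1 point (for example 2.73 − 2.29 = 0.44, with 2.29 = 0.6140 − 0.5911).

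**Conclusion.** The asymmetry is real, and where scans are missed before early loss its effect is upward. It does not shrink with sample size, and no stated analysis covers it. It is nevertheless small: about zero with no early loss or with scans on schedule, roughly 0.2 to 1 point with a 6-week gap and 0.6 to 3 points with a 12-week gap. These ranges rest on assumed losses of 5–20%, exponential PFS and a 55% planning rate; the extreme 40% runs reach 1.8 and 4.1 points.

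Two stronger readings fail. One is that the PFR is certainly biased upward: the document gives neither the early loss nor the missed scans on which that depends. The other is that each affected patient costs 2 points: the expected shift is about 0.3. The 49 per group stands. This is a minor point of definition with a cheap improvement.

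**What to change.** Reword Table 1 item 6 along these lines: *Survivors without progression are censored at the date of the last adequate RECIST tumour assessment showing no progression, or at registration if there was no assessment after baseline.* Report the clinical-date rule as a sensitivity analysis. Once scans are missed the two rules err in opposite directions, so together they bracket the 24-week PFR. With scans on schedule they nearly agree, both slightly low.

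The cost is one sentence and one extra analysis; scan dates are already needed for the response and progression assessments. The downside is slightly shorter censored follow-up, slightly wider intervals and a small downward shift, about 1 to 1.5 points at 20% loss. No change to the sample size is needed.
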